## Abstract

**Background:**

Preventing excessive weight gain during pregnancy is potentially important in the prevention of overweight and obesity among women of childbearing age. However, few intervention studies aiming at weight management during pregnancy have been performed and most of these interventions were not as successful as expected. In this paper the design of the New Life(style) study is described as well as the content of the individually tailored intervention program, which focuses on controlling weight development during pregnancy.

**Methods:**

The effectiveness of the New Life(style) intervention program versus usual care by midwives is evaluated in a randomised controlled trial. Women who expect their first child and visit one of the participating midwifery practices are included. The intervention is standardised in a protocol and executed by trained counsellors with the women who are randomised in the intervention group. During 5 sessions – at 18, 22, 30 and 36 weeks of pregnancy and at 8 weeks postpartum – individual weight gain is discussed in relation to weight gain guidelines for pregnant women of the American Institute of Medicine. Counsellors coach the women to maintain or optimise a healthy lifestyle, in a period of drastic physical and mental changes. Data is collected at 15, 25, 35 weeks of pregnancy and at 6, 26, and 52 weeks after delivery. Primary outcome measures are body weight, BMI, and skinfold thickness. Secondary outcome measures include physical activity, nutrition and blood levels of factors that are associated with energy homeostasis.

**Discussion:**

Results of the current RCT will improve the knowledge of determinants of weight gain during pregnancy, weight retention after childbirth and of the effectiveness of the intervention program that is described. Caregivers and researchers in the field of health promotion are offered more insight in specific elements of the New Life(style) intervention program.

## Background

Over 1.1 billion adults and 10% of children worldwide are now classified as overweight or obese [1]. Because of a substantial adverse impact on health and well-being [2], stabilising or decreasing the number of people with overweight is addressed as a target of many regional and national health programs in developed countries [3]. As different life events can trigger a shift in the energy balance resulting in positive weight changes and a higher risk of developing overweight, these moments are thought to be the moments when people will benefit most from health-promoting activities. Therefore, subgroups such as children who are starting school, retired or sick people, are often the target group of health promoting programs [4].

In this manuscript we elaborate on the New Life(style) project. In this study the focus is on pregnant women, because pregnancy has shown to be an independent risk factor for developing overweight [5-8]. Although the American Institute of Medicine (IOM) developed evidence based guidelines for weight development during pregnancy in 1990, still 20% to 40% of women gain more weight than advised by the IOM [9]. Weight gain during pregnancy is considered to be the most important determinant of postpartum weight retention [10,11]. Studies describe an average weight retention of 2–3 kg, 6 to 12 months after delivery and losing this "extra" weight after having given birth proves to be difficult [12,13]. For this reason, preventing excessive weight gain during pregnancy is important in the prevention of overweight and obesity among women of childbearing age.

Although it has been recognised that pregnancy increases the risk of developing overweight later in life, only few intervention studies aiming at weight management during pregnancy have been performed. Moreover, most of these interventions were not as successful as hoped. Polley et al. [14] were the first to evaluate the effect of a stepped-care, behavioural intervention. They found that the intervention was effective in reducing the incidence of excessive weight gain in normal-weight women, but not in overweight women. No significant effects were found with regard to total weight gain or net weight retention. An intervention study consisting of regular, individual diet counselling, physical activity sessions and other activities related to nutrition was conducted by Gray-Donald et al. [15]. They found only a minor effect on diet, but no effect on weight gain or physical activity. Finally, Olson et al. [16] reported a reduced risk of excessive gestational weight gain in a low-income subgroup of women only. Those women were monitored by health care providers and received patient education by mail.

An intervention program that will be effective for every individual is unrealistic, but it is clear that the need for effective strategies concerning weight management during pregnancy will remain. For this reason, an individually tailored intervention was developed for the study that is discussed in this paper; i.e. the New Life(style) intervention program. The main focus of this intervention is to help pregnant women to gain weight within IOM-guideline limits by 1) informing them on these guidelines, but also on physical activity and nutritional guidelines for pregnant women; 2) reviewing individual lifestyle and 3) giving support to optimise individual lifestyle during pregnancy.

The present paper reports on the methodological design of the New Life(style) study as well as the content of the intervention program. Publishing the design and rationale of an RCT before results are available has important benefits [17]. It is an opportunity to elaborate on the content and background of an intervention program and to consider the methodological quality of the study critically, irrespective of the results. As a consequence, caregivers and researchers in the field of health promotion are offered more insight in specific elements of intervention programs.

## Methods

### Study design

The study is designed as a randomised controlled trial to evaluate the effectiveness of a lifestyle intervention program with the main focus on weight development, physical activity and nutrition habits during pregnancy. The design is presented in Figure 1. The Medical Ethics Committee of VU University Medical Centre has approved the study design, protocols and informed consent procedure. Participating women are assigned at random to the control or to the intervention group. They are studied during a period of 18 months: from 15 weeks of pregnancy until one year after delivery.

### Setting

This trial is carried out in eight midwifery practices in Dutch towns with 23,000–735,000 inhabitants. The midwives working in these practices ask the women to participate in the study from February 2005 until May 2006. By selecting practices in different urbanised agglomerations we aim to include a selection of midwives and participants that is representative of these subgroups in the Western part of the Netherlands. Participation in the study is voluntary.

### Midwifery in the Netherlands

In the Netherlands midwives are independent paramedical practitioners, qualified to provide full maternity care to all women whose pregnancy and childbirth are uncomplicated. The primary task of the Dutch midwife is to follow closely the health status of the pregnant woman and unborn child [18]. The first appointment at the midwifery practice takes place between the 9^th ^and 12^th ^week of gestation. Pregnant women visit the midwives 11–13 times during their pregnancy for about 15 minutes each time. Eventually, thirty percent of births occur at home, assisted by these midwives; seventy percent of pregnant women deliver in hospitals [19]. Because of the frequent contacts throughout pregnancy and because of their expertise, midwives are considered to be important information providers of pregnant women, especially for women without children who visit the midwife for the first time in their lives. For some women midwives have a corrective, reassuring and reinforcing role.

### Rationale for using midwifery practices as the research setting

The unique platform of midwifes that exists in the Netherlands is very appropriate for conducting this trial with pregnant women as the women are recruited for participation by esteemed health care providers, and not via impersonal invitation letters. By individually addressing the women by the midwives we hope to optimise the inclusion of participants. Another advantage of using midwifery practices as the research setting is that the appointments of participants with their midwives can be combined with appointments for research purposes. Extra visits of participants to a research centre are not necessary, reducing the time consuming consequences of an extensive research program with several succeeding measurement moments.

### Recruitment of midwifery practices

Twenty five midwifery practices were approached and invited to participate in this study. Some practices were recruited via personal work-related contacts and others via the phone-book. All practices are within an area of 60 kilometres from the VU University Medical Center in Amsterdam and are accessible by public transport; an accessibility criterion. Furthermore, participating practices have to provide a room once a week, for measurements and the counselling sessions that constitute the intervention program.

The approached practices received a brochure about the study and were called one week later by the research team, to ask for participation. Nine of the twenty five practices were too busy to participate in a study, three practices were not interested in the subject of weight gain during pregnancy, three practices had no spare room, and two already participated in another study.

During the study, there will be no data exchange between researchers and midwives (e.g. group allocation, anthropometric data, content of counselling sessions). Midwives are instructed to refer participants with questions about the study to the research team and to provide usual care to all their clients, irrespective of their participation or randomisation status.

### Study population

#### Sample size

The aim is to include 275 participants in the study. A power analysis has been based on the effects of the intervention program on BMI of participants in the intervention group. In order to be able to detect a clinically relevant difference in BMI of 0.8 kg/m^2 ^at six months postpartum between the intervention and control group, 220 participants are needed, 110 participants in each group. These numbers are based on a power (1-B) of 0.80, a significance level of 5% (two-sided) and a standard deviation of 2.0 kg/m^2^. When a drop out of 20% is taken into account, which is normal for similar research with 1 year follow up, 275 women are needed for this trial.

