### Randomisation

A computerized random number generator draws up an allocation schedule prestratified for midwifery practice; within practices respondents are allocated to the intervention group or to the control group at random. During the first telephone call with the research assistants – 2 weeks after the first appointment with the midwife; at 10–14 weeks of pregnancy – participants are informed about which group they are assigned to.

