### Content of the counselling sessions

Each counselling session is structured in a uniform way (see Table 1). During the first visit the counsellor talks about weight gain during pregnancy and the distribution of this 'extra' weight among different tissues. After this, the IOM guidelines are introduced and the dependence of healthy weight gain during pregnancy on pre-pregnancy body mass index is discussed. Weight and height is assessed and pre-pregnancy BMI is calculated, after asking for pre-pregnancy weight, in order to categorize women in pre-pregnancy BMI-groups: underweight, normal weight, overweight or obese.

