### Blood samples

In order to study the influence of lifestyle factors on energy homeostasis and weight gain, blood samples are taken intravenously from a subgroup of participants during each measurement. The midwives also take a blood sample from the umbilical cord. Blood is processed and stored at the laboratory of the VU University Medical Centre, so that – after selecting subgroups of normal and high gainers – blood levels of leptin, ghrelin, fasting insulin/glucose, insulin growth factor 1, insulin growth factor binding protein 1 and 3, and cortisol can be measured.

By means of the questionnaires, data are also collected on: perceived health, stage of change with regard to weight management, physical activity and diet according to the model of Prochaska, and behavioral determinants such as attitude, social support, self efficacy with regard to weight management, physical activity and nutrition. Possible confounders that are assessed include: age, age at menarche, education, ethnicity, marital status, smoking behaviour and individual health status, including complications during pregnancy, the duration of labour and possible complications during or after delivery.

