### Statistical analyses

Analyses will be performed to estimate the effect of the intervention on five domains: 1) total weight gain during pregnancy 2) the percentage of women gaining weight above the recommended IOM guidelines; 3) weight retention at six months and one year postpartum; 4) physical activity levels; and 5) behavioral determinants of weight management, physical activity and nutrition.

Longitudinal logistic regression analysis will be used for dichotomous outcome measures, and longitudinal linear regression analyses will be performed for all other outcome measures. In these analyses, the correlation between multiple measurements within one individual is taken into account. The regression coefficient reflects the average difference in the outcome variable between conditions. Possible confounders will be entered into the regression analyses. Confounding will be defined as a change in the regression coefficient of 10% or more. Possible effect modification will be studied as well, defined as a significant (p <0.10) interaction-term between group allocation and the variable concerned. Datawill be analysed according to the intention-to-treat principle and the per protocol principle.

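### The sample-size paragraph does not say what the BMI SD of 2.0 kg/m² measures, and the stated analysis names neither baseline BMI nor midwifery practice as a covariate, so power for a comparison of BMI level is uncertain.

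*Protocol article*

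**What the plan says.** All references are to the Methods of the protocol article.

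- **Sample size.** The target is a "clinically relevant difference in BMI of 0.8 kg/m"² at six months postpartum. The result is that "220 participants are needed, 110 participants in each group". "These numbers are based on a power (1-B) of 0.80", with "a significance level of 5% (two-sided) and a standard deviation of 2.0 kg/m"². No source or definition of the SD is given. A 20% dropout allowance raises the total to 275.
- **Selection of participants** lists three eligibility criteria, none of them about BMI. **Content of the counselling sessions** has counsellors take weight and height "in order to categorize women in pre-pregnancy BMI-groups: underweight, normal weight, overweight or obese".
- **Randomisation** uses an "allocation schedule prestratified for midwifery practice". Women learn their group by telephone at 10–14 weeks. The baseline measurement is at 15 weeks (Measurements), and counselling starts at 18 weeks (Intervention).
- **Blood samples** holds the list of candidate covariates: "Possible confounders that are assessed include: age, age at menarche, education, ethnicity, marital status, smoking behaviour and individual health status", followed by pregnancy and delivery complications. Baseline or pre-pregnancy BMI and practice are not on it.
- **Statistical analyses** plans longitudinal linear regression for continuous outcomes. "In these analyses, the correlation between multiple measurements within one individual is taken into account". The group coefficient is the average difference in the outcome. A covariate counts as a confounder if it moves that coefficient by 10% or more. Two of the five analysis domains are total weight gain and postpartum weight retention.

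**The concern.** The power statement concerns a difference in BMI level between groups. In women recruited without a BMI limit, most of the spread in BMI six months after delivery is likely to be spread that was already there before pregnancy. An SD of 2.0 puts about 95% of women within roughly 8 BMI units. That is narrow for a sample expected to run from underweight to obese, but plausible for change in BMI or for BMI given its starting value.

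The analysis section does not commit to either of those. Allowing for correlation between a woman's repeated measurements does not in itself remove stable differences between women from a comparison of group levels. Whether baseline BMI enters at all is left to a rule that reacts to chance imbalance rather than to how strongly a covariate predicts the outcome.

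At stake is precision for the outcome on which the trial was sized. A second and smaller matter is that practice is not named in the model, although it stratifies the allocation and each measuring assistant is tied to particular practices.

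**Working it through.** **1. The plan's own figure.** Inputs from Sample size: difference 0.8, SD 2.0, two-sided 5%, power 80%.

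n per group = 2 × (1.960 + 0.842)² × (2.0/0.8)² = 2 × 7.849 × 6.25 = 98.1, so 99. The t-test version gives 99.1, so 100. The stated 110 is not reproduced. At 110 per group:

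- SE = 2.0 × √(2/110) = 0.270, and power is 84.0% (t-test) or 84.3% (normal approximation).
- The SD for which 110 per group gives exactly 80% is 0.8 × √55 / 2.802 = 2.12 (normal approximation).
- The dropout step is right: 220/0.80 = 275.

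The stated size is therefore about 11% above what its inputs require, which errs on the safe side.

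**2. Does 2.0 look like a raw SD?** Assume normality, a mean BMI of 23 to 25 and an obesity cut-off of 30; none of these is in the document. With SD 2.0, the share at or above 30 is 1 − Φ(7/2) = 0.02% for mean 23 and 1 − Φ(5/2) = 0.6% for mean 25. That is at most about two women in 275, which sits badly with a programme that has a separate obese group. It is an indication, not proof.

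**3. What else could 2.0 be?** For an assumed raw SD s and baseline correlation r, the residual SD after baseline adjustment is s√(1 − r²), and the SD of change (equal variances) is s√(2(1 − r)). Setting each to 2.0:

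| Assumed raw SD | r needed, adjusted | r needed, change |
|---|---|---|
| 3.0 | 0.75 | 0.78 |
| 3.5 | 0.82 | 0.84 |
| 4.0 | 0.87 | 0.88 |
| 4.5 | 0.90 | 0.90 |

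The two readings fit about equally well.

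**4. Power at 110 per group for a difference of 0.8** (two-sample t-test at one time point):

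| SD of BMI (all but 2.0 assumed) | Unadjusted | Adjusted, assumed r = 0.90 (residual SD) |
|---|---|---|
| 2.0 (stated) | 84.0% | – |
| 2.5 | 65.6% | – |
| 3.0 | 50.4% | – |
| 3.5 | 39.3% | 97% (1.53) |
| 4.0 | 31.5% | 92% (1.74) |
| 4.5 | 25.9% | 85% (1.96) |

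The normal approximation gives slightly higher unadjusted figures, for example 31.7% at SD 4.0. Unadjusted power passes below 80% at an SD of about 2.1.

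**5. Would the 10% rule bring baseline BMI in?** Simulating 110 per group, a true difference of 0.8 and r = 0.90, with baseline BMI as a candidate, adding it moved the coefficient by at least 10% in about 85% to 88% of trials for SDs of 3.5 to 4.5. In the other 12% to 15% it is dropped. In the same setting, power under the rule was 88% / 83% / 76% for SD 3.5 / 4.0 / 4.5, against 97% / 92% / 85% when adjustment is always made.

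**6. Practice.** If practice explains a share ρ of the variance, leaving it out widens the standard error by 1/√(1 − ρ): 1.026 at ρ = 0.05 and 1.054 at ρ = 0.10 (both assumed).

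**The case against.** The strongest reply has four parts.

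- **No raw SD is given.** A reader might infer that 2.0 can only be a baseline-adjusted SD. The document does not support that. It gives no raw figure, a change score fits 2.0 about as well, and the BMI groups serve to choose a weight-gain chart rather than to describe an expected distribution. This part stands.
- **Change outcomes are analysed.** Weight gain and weight retention already subtract a starting weight, so much of the stable variance is gone for those domains. This stands too, but the power calculation is for BMI level, and BMI, weight and skinfolds are the named primary outcomes.
- **Silence is not refusal.** A reader might infer that the plan rules out adjusting for baseline or practice. It does not: the confounder list is open, either could enter, and a full protocol or SAP may say more. The accurate statement is that neither is named. What remains is a fault in something the article does state: a 10% rule is a poor gate for a strong predictor in a randomised comparison, because it drops that predictor when the arms happen to be balanced.
- **The model is longitudinal.** The power figures above are for one time point, and the article does not say how baseline and time enter. So it cannot be concluded that 80% power is lost. Repeated measures alone would help little, however: averaging two postpartum values with an assumed correlation of 0.90 shrinks the SD only by √(1.90/2) = 0.975.

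On practice, stratified allocation already balances it across arms, and ignoring it is conservative. That part is a small efficiency gain only.

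**Conclusion.** The point holds as one of unclear specification and avoidable loss of precision. It does not establish that the trial is underpowered.

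Two things follow from the document alone. The SD of 2.0 is undefined and unsourced, and the stated inputs give 99 to 100 per group for 80% power, or about 84% power at 110. The rest is conditional. If BMI level is compared without baseline, power drops below 80% once the SD exceeds about 2.1, and to between two thirds and one third over assumed SDs of 2.5 to 4.0. Adjustment recovers it, to 97% at SD 3.5 and 92% at 4.0, if the baseline correlation is near an assumed 0.90. The change outcomes are less affected. The gain from practice is small: standard errors about 3% to 5% too wide if practice explains an assumed 5% to 10% of variance.

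Always adjusting is better than the stated rule and nearly free, so the change is worth making even though the size of the loss is not known.

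**What to change.** 1. **Statistical analyses:** for BMI, weight and skinfolds, always include the 15-week value of the same outcome, and midwifery practice as a fixed factor, whatever the 10% rule shows.
2. **Timing of baseline:** state that the 15-week value is taken after women learn their allocation (10–14 weeks) but before counselling begins (18 weeks). Repeat the analysis with pre-pregnancy BMI as covariate for sensitivity, noting that it rests on self-reported weight.
3. **Sample size:** state whether 2.0 is the SD of raw BMI, of change or of the baseline-adjusted residual, and give its source. The authors should report what it is; it should not simply be relabelled to fit the model.
4. **Arithmetic:** say that the stated inputs need 99 to 100 per group and that 110 gives about 84% power, or give the inputs that lead to 110.

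Cost: two sentences and about 8 degrees of freedom (seven for eight practices, one for baseline), using data already planned for collection.

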### Selection of participants

Subjects participating in the study are recruited by participating midwives. During the intake, midwives invite women who are expecting their first child to participate. They introduce the study to the new client and give the women who are interested a brochure about the trial, to be read at home. After having received consent to do so, midwives write the name, telephone number, body weight, and expected date of delivery of interested women on a reply coupon, and send this coupon to the research team. Subsequently, a research assistant calls interested women within two weeks after the introduction to the study by her midwife. During this conversation the aim and implications of the study are explained again and the eligibility criteria are checked. Women are eligible for participation when they are:

1) expecting their first child;

2) able to read, write and speak Dutch;

3) within their first 14 weeks of pregnancy.

When a woman meets these inclusion criteria and wishes to join the study, she is included. After inclusion, an appointment is made for the baseline measurement at the midwifery practice. Informed consent forms will be obtained from each participant.

This study focuses on women who are expecting their first child, and who will deliver their first child during the term of the study. By excluding pregnant women who already have children, the study population is expected to be more homogeneous. Mothers that are expecting their second or third child, have already experienced at least one pregnancy and the weight change related to that pregnancy. Based on the experiences in their previous pregnancy, these women already have specific expectations and attitudes concerning weight changes and lifestyle during pregnancy. Besides, the daily situation of women with children is different. Because of the transition from a household of adults to a family life, their lifestyle has already been changed. So, focusing on women without children limits disturbing effects of parity on outcome measures.

